**Baseline information**							
Informed consent	√						
Eligibility screen			√				
Medical history	√						
Allocation	√						
**Effectiveness observation**							
Blood pressure	√		√	√	√	√	√
24-h blood pressure			√				√
Pro-inflammatory/anti-inflammatory cytokines			√				√
Improvement in TCM syndrome			√	√	√	√	√
Improvement in quality of life			√				√
Pharmacogenomic evaluation			√				√
**Safety observation**							
Physical exam		√					√
Blood pressure		√					√
Routine blood test		√					√
Routine urine test		√					√
Liver and kidney function		√					√
Adverse event				√	√	√	√
**Other work**							
CRF audit							√

### Adverse events

Any accident, any signs of discomfort, or any disease symptoms, such as severe pain, syncope, hematoma, bleeding, or hypertensive emergencies, will be viewed as adverse events and will be recorded on the participant’s CRF. The research leader, sponsor, and the ethics committee will be contacted within 24 h, if the clinical researchers report an adverse event, and the ethics committee will recommend relevant treatment.

### Statistical analysis

#### Sample size calculation

The formula used to calculate the sample size is as follows, which is based on superiority clinical trial interval hypothesis test sample size estimation [52]. The sample size was calculated based on the expected reduction in reducing of BP. One previous study suggested that the reduction of BP after interventional treatment is 4.5 mmHg, and the BP SD is 10 mmHg. Therefore, we assume the reduction of BP as 4.5 mmHg in this study. In the following formula, *c* is the ratio between two sample cases, *n*1 = *n*2, so *c* = 1. *σ* is the BP SD 10 mmHg, and *δ* is the expected effect BP 4.5 mmHg, so *σ* = 10 and *δ* = 4.5. Given a type I error rate of *α* = 0.05, a power of 90% (type II error rate of *β* = 0.1), so *uα* = 1.96, *uβ* = 1.282. *n1* = *n2* ≈ 104, the sample size for one group needs to be 104, resulting in *n* = 2 × 104 = 208 patients. Considering the maximum possible dropout rate is 20%, a total of 260 patients needs to be allocated to reach the required number of patients for the efficacy analysis.
$$ {\displaystyle \begin{array}{c}{n}_1={\left[\frac{\left( u\alpha + u\beta \right)\sigma }{\delta}\right]}^2\frac{\left(1+c\right)}{c},{n}_2=c{n}_1\\ {}{n}_1={n}_2\approx 104\end{array}} $$

#### Planned data analysis

The intention-to-treat principle will be used to analyze the efficacy and safety of BSJY. The independent data administrator and the professional statistician will undertake data entry and data management, and perform the data analysis, respectively. All the efficacy and safety analyses with all randomly assigned participants included will be conducted within the full analysis set (FAS). The per-protocol set (PPS) analysis will also be conducted to compare the results from FAS and PPS. Demographic and laboratory characteristics will be calculated at baseline and after the treatment period for all patients. The statistical analysis will be done at Guang’anmen Hospital, China Academy of Chinese Medical Sciences in Beijing.

For continuous variables with normal distribution, the comparability of the characteristics between the two study groups will be assessed by using the *t*-test. While for the comparison of data with non-normal distribution, the non-parametric Mann-Whitney-Wilcoxon test will be used. Continuous variables will be expressed by mean ± SD. We will assess the paired *t*-test to compare the difference of the outcome between preintervention and postintervention in each group by using the independent *t*-test. A *χ*^2^ test will be used for categorical variables, while the Fisher exact test will be used when the theoretical frequency is less than 5 in more than 25% of the cells. Categorical variables will be shown as counts and percentages. Whether the hypothesis of superiority is available will be judged by comparing the 95%CI of the difference in intergroup efficacy. All statistical tests are unilateral tests; *p* < 0.05 is statistically significant. All statistical analyses will be performed using SPSS V.20.0.

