**Methods and analysis:**

This trial is a one-center, randomized, double-blind, placebo-controlled study. A total of 260 participants will be randomized in a 1:1 ratio to an experimental group (BSJY plus amlodipine) and a control group (placebo plus amlodipine). The trial cycle will last 8 weeks. The primary outcome is the change in 24-h average systolic and diastolic blood pressure. The secondary outcomes include heart rate variability, pharmacogenomic evaluation, improvement in TCM syndrome, and serum pro-inflammatory/anti-inflammatory cytokines between the two groups. The safety of medication will also be evaluated. All the data will be recorded in electronic case report forms and analyzed by SPSS V.22.0.

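### Safety is fixed as intention to treat in all randomised participants, so anyone never dosed would count in the adverse-event denominator (minor)

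*Protocol article*

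**What the plan says.** The section Planned data analysis applies one principle to both kinds of outcome: "The intention-to-treat principle will be used to analyze the efficacy and safety of BSJY". It then names the population: "All the efficacy and safety analyses with all randomly assigned participants included will be conducted within the full analysis set (FAS". The only other set is for a sensitivity comparison: "The per-protocol set (PPS) analysis will also be conducted to compare the results from FAS and PPS". Nowhere does the article limit safety to participants who took trial medication, or group them by what they received.

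Two places bear on whether a randomised participant could go undosed:

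- **Table 2, baseline information.** Allocation is ticked at day -7. The row "Eligibility screen" is ticked at day 0.
- **Data collection and management.** An enrolment evaluation takes place at day -7. A visit at allocation follows, then visits every two weeks, with 0 days heading the list in brackets. This can be read as placing allocation at day 0.

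**The concern.** For efficacy, keeping everyone as randomised protects the comparison, and any attenuation is conservative. For safety the direction reverses. A person who took no trial medication cannot have an event caused by it, so including that person lowers the reported rate and narrows the absolute difference between arms. That favours the test product.

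Safety of the granules added to amlodipine is a declared evaluation of this trial, and the Discussion promises high-powered evidence on it. The rule is also stated outright. It is not a detail left open for a separate analysis plan, which could add a treated set for safety only by departing from this text.

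**Working it through.** **Size of the arms.** Inputs from Sample size calculation: "the reduction of BP after interventional treatment is 4.5 mmHg, and the BP SD is 10 mmHg"; "Given a type I error rate of *α* = 0.05, a power of 90" per cent; quantiles 1.96 and 1.282.

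- n per arm = 2 × [(1.96 + 1.282) × 10 / 4.5]² = 103.8, rounded up to 104. Both arms: 208.
- With 20% dropout: 208 / 0.8 = 260, as stated ("Considering the maximum possible dropout rate is 20%, a total of 260 patients needs to be allocated"). At 1:1 this is 130 per arm.

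The stated figures reproduce. They serve here only to give the denominator of 130.

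**Can a randomised participant go undosed?** If Table 2 holds, yes. Physical examination, routine blood and urine tests, and liver and kidney function are ticked at day -1, and eligibility at day 0. Severe liver, kidney and haematopoietic disease are exclusions. Results that could exclude someone would thus arrive after a day -7 allocation. Adverse events are ticked only from week 2, so a person who left before day 0 would have no scheduled adverse-event assessment but would still be in the denominator. If allocation is at day 0, this route largely closes.

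**Effect on rates.** Let f be the never-dosed share, with no events counted in those people:

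rate in all randomised = rate in dosed × (1 − f)

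Assumption, not from the documents: 10% (granules arm) and 5% (control) among those dosed, with f equal in both arms.

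| Never dosed per arm | 1 − f | Rates shown | Difference (points) |
|---|---|---|---|
| 0 of 130 | 1.000 | 10% v 5% | 5.00 |
| 1 of 130 | 0.992 | 9.92% v 4.96% | 4.96 |
| 5% | 0.950 | 9.5% v 4.75% | 4.75 |
| 13 of 130 | 0.900 | 9.0% v 4.5% | 4.50 |
| 26 of 130 | 0.800 | 8.0% v 4.0% | 4.00 |

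The last row uses the whole 20% dropout allowance. It is an outer bound, not an expectation.

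**Effect on the comparison.** The risk ratio is 10/5 = 2 in every row, because the factor cancels. The pooled two-proportion statistic is z = difference / √[p(1 − p) × 2/n], where p is the mean of the two rates:

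- f = 5%, dosed only (n = 123.5 per arm): 0.05 / √(0.075 × 0.925 × 2/123.5) = 1.49.
- f = 5%, all randomised (n = 130): 0.0475 / √(0.07125 × 0.92875 × 2/130) = 1.49.
- f = 20%, dosed only (n = 104): 0.05 / √(0.075 × 0.925 × 2/104) = 1.37.
- f = 20%, all randomised (n = 130): 0.04 / √(0.06 × 0.94 × 2/130) = 1.36.

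So the reported rates and their absolute difference shrink, while the test barely moves.

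**The case against.** The strongest reply is that the rule may do no harm. The text on data collection can be read as allocating at day 0. If dosing then starts at once, almost nobody is randomised and undosed. The Trial status section reports 80 participants recruited and through follow-up and gives no sign of undosed participants, though its wording is too loose to settle the matter. Even where dilution occurs, the calculation above shows the ratio and the test hardly change. All of this stands, and it limits the point to the reported rates and the absolute difference.

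Four stronger readings are tempting, and the documents do not support them:

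- **That some participants will go undosed.** Table 2 and the text conflict on the day of allocation, so this is possible but not established.
- **That up to 20% go undosed.** The 20% is dropout over the whole trial. A person who leaves after one dose would still be in a treated safety set.
- **That wrongly supplied participants will be counted in the wrong arm.** This would follow under analysis by assigned arm, but nothing suggests such errors are expected. The article says the manufacturer labelled the packages with the random codes.
- **That the safety laboratory results are diluted too.** They are taken at baseline and at the end of treatment. A person who left before dosing would normally have no end value to enter.

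It might also be said that the per-protocol set already covers the need. It does not. If, as is usual, it leaves out those who meet the withdrawal criteria, it drops people who did not complete treatment, possibly because of an adverse event. Neither named set consists of everyone exposed.

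**Conclusion.** The point holds as a minor one. The article fixes safety on all randomised participants, and no other set it names serves as a treated population. Any never-dosed participants lower each arm's adverse-event rate and the absolute risk difference in proportion to their share: by 0.8% in relative terms for 1 of 130, and by 5% if 5% are undosed. With equal shares in the two arms the risk ratio is unchanged and the test almost unchanged. The effect is zero if every participant is dosed.

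The actual size cannot be fixed from the documents, which give no adverse-event rates and no expected number undosed. The 10% and 5% rates and the shares above are assumptions for illustration.

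**What to change.** Replace the rule for safety with one sentence. The safety set is all randomised participants who took at least one dose of any trial medication, granules or trial amlodipine, grouped by the granules actually received, or by assigned arm if none were taken. Use it for adverse events and for the safety laboratory tests, and keep the all-randomised full analysis set for efficacy.

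The set should not be limited to those who took granules. Participants enter on no antihypertensive drug and amlodipine is trial treatment in both arms, so someone who took only amlodipine has been exposed.

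The change needs no new participants and leaves 104 per arm and 260 in total as they are. It relies only on the record of medication taken, and compliance is already assessed at visits. The article says that no analysis had been done at submission. If that is still so, the change can be made without knowledge of results. The conflict over the day of allocation should be reconciled separately.

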### Endpoint measurements

#### Primary outcome

The primary outcome is the change in 24-h average systolic and diastolic BP, 24-h coefficient of BP variability (CV), morning BP, 24-h BP trough/peak ratio (T/P), 24-h BP smoothing index (SI) [49].

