### Data collection and management

The case report form (CRF) will be used for recording the process for each participant. In addition to the enrollment evaluation (− 7 ± 0 days), each participant will attend an evaluation visit when allocated and every 2 weeks afterwards during the trial (0 days, 2 weeks, 4 weeks, 6 weeks, and 8 weeks). The assessments including physical examination, improvement in symptoms, compliance with medications, questions about adverse events will be given to each participant. Blood tests and 24-h BP monitoring will be evaluated only at the enrollment and close-out visits. The schedule of enrollment, interventions, and assessments can be checked in Table 2. All researchers involved in data entry and data management will sign a confidentiality agreement to prevent data leakage. The personal information of all participants will be carefully protected, and the original CRF will be kept for 5 years after the end of the trial.

**Table 2 Tab2:** Schedule of the data collection

Process/item	Run-in period	Run-in period	Pre-treatment	Treatment period			
Time point	− 7 day	− 1 day	0 days	2 weeks	4 weeks	6 weeks	8 weeks

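### The between-arm test of 24-h blood pressure is not clearly fixed, and baseline enters only by subtraction rather than as a covariate, which costs precision

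*Protocol article*

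**What the plan says.** The Primary outcome section sets a change score: "The primary outcome is the change in 24-h average systolic and diastolic BP", followed by further BP indices. The 24-h recording is made twice per patient. Data collection and management says "Blood tests and 24-h BP monitoring will be evaluated only at the enrollment and close-out visits", and in Table 2 the row "24-h blood pressure" is ticked at day 0 and week 8.

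For continuous data, Planned data analysis has three relevant sentences:

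- A t-test for normally distributed variables, introduced as a check that the two groups' characteristics are comparable.
- Its continuation: "While for the comparison of data with non-normal distribution, the non-parametric Mann-Whitney-Wilcoxon test will be used".
- The only sentence that attaches a t-test to the outcome. It proposes a paired t-test "to compare the difference of the outcome between preintervention and postintervention in each group by using the independent" t-test.

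The same section judges superiority from the 95% CI of the between-group difference in efficacy. No baseline-adjusted model is named.

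The sample size section cites a previous study in which "the reduction of BP after interventional treatment is 4.5 mmHg, and the BP SD is 10 mmHg". It carries both figures forward at "a power of 90% (type II error rate of" 0.1), giving 104 per group.

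**The concern.** A paired t-test and an independent t-test answer different questions, and one sentence cannot assign both to the same pre/post comparison within each group. Read as paired within arms, it gives two p-values that are not randomised comparisons. Entrants take no antihypertensive drugs (Inclusion criteria) and both arms then start amlodipine, so both are expected to fall whether or not BSJY adds anything. Read as independent between arms, it is a valid comparison of changes, but that is not what the sentence says.

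Two further matters follow. Every test named is unadjusted, so the baseline recording serves only as something to subtract. If the rank-test sentence also governs efficacy, the test would depend on how the data look, and a Mann-Whitney test does not supply the mean-difference CI that the superiority rule and the mean-based sample size point to. At stake are an unambiguous primary analysis and precision that costs nothing to recover.

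**Working it through.** **1. Reproduce the plan's figure.** Inputs from Sample size calculation: δ = 4.5 mmHg, σ = 10 mmHg, u-values 1.96 and 1.282, ratio 1:1.

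n per arm = 2 × [(1.96 + 1.282) × 10 / 4.5]² = 103.8, so 104. Two arms give 208, and 208 / 0.80 = 260. The stated figures reproduce.

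Power at 104 per arm, two-sided 0.05: SE = 10 × √(2/104) = 1.387; 4.5 / 1.387 = 3.245; Φ(3.245 − 1.96) = 90.1%.

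**2. Variance with and without the covariate.** Let s be the SD of a single 24-h mean, taken as equal at both visits, and r the baseline to week-8 correlation. The protocol does not give r, so a range is shown.

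- Unadjusted change: variance 2s²(1 − r).
- ANCOVA on baseline: residual variance s²(1 − r²).
- Ratio, ANCOVA to change: (1 + r)/2, which is below 1 for every r below 1.

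**3. If 10 mmHg is the SD of change.** ANCOVA SD = 10 × √((1 + r)/2). Power = Φ(4.5 / (SD × √(2/104)) − 1.96).

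| r | ANCOVA SD | Power, unadjusted | Power, ANCOVA | n per arm for 90% with ANCOVA |
|---|---|---|---|---|
| 0.3 | 8.06 | 90.1% | 98.1% | 68 |
| 0.5 | 8.66 | 90.1% | 96.3% | 78 |
| 0.7 | 9.22 | 90.1% | 94.1% | 89 |
| 0.8 | 9.49 | 90.1% | 92.8% | 94 |

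**4. If 10 mmHg is the SD of a single BP value.** Change SD = 10 × √(2(1 − r)); ANCOVA SD = 10 × √(1 − r²).

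| r | Change SD | Power, unadjusted | n per arm for 90%, unadjusted | ANCOVA SD | Power, ANCOVA | n per arm for 90%, ANCOVA |
|---|---|---|---|---|---|---|
| 0.3 | 11.83 | 78.3% | 146 | 9.54 | 92.5% | 95 |
| 0.5 | 10.00 | 90.1% | 104 | 8.66 | 96.3% | 78 |
| 0.7 | 7.75 | 98.7% | 63 | 7.14 | 99.5% | 53 |

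**5. What within-arm tests would show.** Suppose BSJY adds nothing, the SD of change is 10, there are 104 per arm, and both arms truly fall by D mmHg. Each paired test is significant with probability p = Φ(D / (10/√104) − 1.96). Exactly one arm is significant with probability 2p(1 − p).

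| D (assumed) | p | Exactly one arm significant |
|---|---|---|
| 2 | 53% | 50% |
| 3 | 86% | 24% |
| 5 | 99.9% | 0.2% |

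With a sizeable amlodipine effect both arms are almost surely significant. With a small one, a discordant pair is common. Neither pattern says anything about BSJY.

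**The case against.** The strongest reply is that little here is wrong in substance.

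- A reader might infer that baseline 24-h BP goes unused. It does not: the primary outcome is a change, so baseline enters by subtraction. The accurate statement is that it is not adjusted for as a covariate.
- A reader might infer bias or a raised type I error. In a randomised trial an unadjusted comparison of changes has neither. Only precision is lost, and if 10 mmHg is the SD of change the planned 90% power is met without ANCOVA.
- A reader might infer that within-arm p-values will decide efficacy. The stated rule is a CI for the between-group difference, and nothing in the article says that a within-arm result will support a claim about BSJY.
- A reader might infer that an unadjusted t-test or a rank test is definitely planned for the primary endpoint. Those two sentences concern comparability of the groups, so the efficacy test is unclear rather than clearly unadjusted.
- A reader might take the contradictory sentence literally, as an independent test on the same patients' before and after values, with an inflated standard error. Paired within arms and independent between arms is the likelier intention, so no weight is put on that reading.
- A model statement may stand in an analysis plan that is not shown, so the absence of ANCOVA would be weak as a finding by itself. A mean-difference CI can also be reported whichever test supplies the p-value.

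All of this narrows the point. It does not repair the sentence, which is contradictory as printed, and it does not make the tests that are named the best use of the two recordings.

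**Conclusion.** The point holds in limited form, as something that should be fixed. The printed text does not clearly fix the between-arm test of the primary endpoint, and the tests it names leave baseline 24-h BP out as a covariate.

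The loss is one of precision. It is about 3 to 8 power points if 10 mmHg is the SD of change (r from 0.8 to 0.3). If 10 mmHg is the SD of a single reading, it runs from under 1 point (r = 0.7) to about 14 (r = 0.3); at r = 0.3 an unadjusted change score would need 146 per arm against the planned 104. The gain rests on assumed correlations and equal variances at the two visits, but its direction is the same at every r examined.

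The figures use two-sided 0.05, which is what the sample size's 1.96 implies. Planned data analysis calls all tests one-sided; that is a separate inconsistency and does not change the ordering of the methods. The documents do not support the claim that the trial's conclusion would be biased or would rest on within-arm tests.

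**What to change.** Replace the contradictory sentence with one pre-specified between-arm analysis: ANCOVA of week-8 24-h mean SBP on treatment arm with the baseline 24-h mean SBP as covariate, and likewise for DBP. Report the adjusted difference with a two-sided 95% CI whatever a normality test shows, and tie the superiority rule to that interval. Keep rank tests as sensitivity analyses and present within-arm changes descriptively, without using them as evidence of efficacy. State also whether the 10 mmHg in the sample size is the SD of change or of a single value.

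The cost is a rewritten paragraph and one model statement in SPSS. No new data are needed, since both recordings are already scheduled. Trial status reports that recruitment was continuing and that no analysis had been conducted, so on that account the change could be made and dated before any results were known.

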Traditional Chinese medicine (TCM) has long been widely used in hypertension in China. *Huangdi Neijing*, a classic work on TCM, classified hypertension as headaches and vertigo. Nowadays, numerous studies have demonstrated the biological activity and therapeutic mechanism of TCM in hypertension [14, 15]. Bu-Shen-Jiang-Ya granule (BSJY) is composed of eight herbs, Dihuang (Radix Rehmanniae Glutinosae), Shanzhuyu (Corni Fructus), Duzhong (Cortex Eucommiae Ulmoidis), Tianma (Gastrodiae Rhizoma), Sanqi (Notoginseng Radix), Mudanpi (Cortex Radicis Moutan), Shanzha (Crataegi Fructus), and Zexie (Rhizoma Alismatis), which is made from a modification of the classical Chinese herbal formula Liuwei Dihuang pill (Table 1). Our previous studies show that BSJY has a clinical effect on patients suffering from kidney-yin deficiency syndrome type hypertension [38–40]. The experimental acute toxicology study showed that the safety of BSJY is reliable [41]. Besides, BSJY reversed hypertensive ventricular hypertrophy by regulating the ERK pathway and protected the endothelial function by regulating the PI3K/Akt pathway [42]. However, the pharmacogenomic evaluation of antihypertensive responses of BSJY remains unclear. This study is designed to investigate whether BSJY may represent a potential remedy for decreasing BP and slowing disease progression in low-to-medium-risk hypertension based on pharmacogenomic evaluation. If positive, this work will be the first one that provides an evidence-based medicine remedy for TCM on treating hypertension by pharmacogenomic evaluation.

**Table 1 Tab1:** Components and dose of BSJY

Chinese name	English name	Latin name	Origin	Main ingredients	Main pharmacological effects	Raw drug weight (g)	Granule weight (g)
Duzhong	Eucommia bark	Cortex Eucommiae Ulmoidis	The bark of Cortex Eucommiae Ulmoidis	Quercetin; Mairin; beta-sitosterol; kaempferol; Erythraline; Eucommin A; (-)-Tabernemontanine; cyclopamine; GBGB; helenalin	Lowering BP [16]; reversing hypertensive vascular remodeling and hypertensive cardiac remodeling [17]; improving insulin resistance and lowering blood glucose [18]	10	0.48
Dihuang	Rehmannia	Radix Rehmanniae Glutinosae	The root of Radix Rehmanniae Glutinosae	EIC; sitosterol; stigmasterol; aeginetic acid; jioglutin D; rehmaglutin B	Lowering BP and improving insulin resistance [19] glucose metabolism, lipid metabolism [20]	25	3.57

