## Methods and design

### Objectives

Our study aims to assess the clinical effect of BSJY on pharmacogenomics and pro-inflammatory/anti-inflammatory cytokines in patients with low-to-medium-risk hypertension, to firstly provide a preliminary pharmacogenomic evaluation of antihypertensive responses in hypertension, and to observe whether TCM plus Western medicine has a better curative effect than Western medicine alone.

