#### Secondary outcomes

The following are the secondary outcomes:
Heart rates variability, based on routine 24-h BP monitoringAssessment of any improvement in TCM Syndrome, using TCM Syndrome Integral Scale (Additional file 2). In this scale, the score of the symptom will be based on the severity, duration, and frequency of the symptoms: 0 points means the symptom did not appear in the past 1 month, 1 point means the symptoms are mild or the frequency of attacks is low, 2 points means the symptoms are moderate or the frequency of attacks is moderate; and 3 points means the symptoms are very severe or the symptoms constantly puzzled. The TCM therapeutic effect Index (TCMTEI), as calculated with the following formula, will be used to evaluate the treatment efficacy in the TCM syndrome.
$$ \mathrm{TCMTEI}=\left(\frac{\mathrm{symptom}\ \mathrm{score}\ \mathrm{before}\ \mathrm{treatment}-\mathrm{symptom}\ \mathrm{score}\ \mathrm{after}\ \mathrm{treatment}\ }{\mathrm{symptom}\ \mathrm{score}\ \mathrm{before}\ \mathrm{treatment}}\right)\times 100\% $$Assessment of any improvement in quality of life, using the 36-Item Short Form Health Survey [50, 51].Changes in levels of blood lipids, including total cholesterol, triglycerides, low-density lipoproteins, and high-density lipoprotein.Serum pro-inflammatory/anti-inflammatory cytokines in patients: changes in the serum levels of TNFα, IL2R, IL6, IL8, IL10, and IL1β will be assessed at baseline and treatment endpoint.Pharmacogenomic evaluation: twenty loci/SNPs associated with BP/hypertension will be assessed at baseline and treatment endpoint.Safety evaluation: routine blood and urine test including levels of creatinine, blood glucose, and homocysteine will be assessed at baseline and treatment endpoint.

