Pharmacogenomic evaluation of antihypertensive responses offers the clinical promise of individualization of therapy based on a person’s genetic makeup [11]. It is said that the loci/SNPs associated with BP/hypertension are also associated with BP response to antihypertensive drugs [10]. This is the first paper that researches pharmacogenomic evaluation of antihypertensive responses in TCM. The present study is designed as a double-blind, randomized, placebo-controlled trial that will provide high-powered evidence regarding the efficacy, safety, and pharmacogenomic evaluation of BSJY in treating patients with low-to-medium risk hypertension. The progress and quality of the trial will be monitored by a clinical research organization of Guang’anmen Hospital.

There are also some limitations to this study. First, we supposed to test twenty single nucleotide polymorphisms (SNPs) that have been associated with BP in genome-wide association studies in Asian people. It is different that significant genetic loci for BP and hypertension reported in genome-wide association studies in Europeans, Asians, and Africans. It should be considered that the complexity of the genetic mechanisms underlying hypertension and the need for much larger sample sizes when looking for genes associated with BP. For TCM, it can be viewed as a very important environment element to pharmacogenomic evaluation. Second, our multi-center experiments will be conducted in China in the future.

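### One uncorrected p < 0.05 rule covers every test, including the twenty SNPs and six cytokines named in the aim, and the article's claim of high power for pharmacogenomics conflicts with its own caveats and its BP-only sample size

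*Protocol article*

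**What the plan says.** The Planned data analysis section applies one criterion to every test: "All statistical tests are unilateral tests; *p* < 0.05 is statistically significant". The same section also says that superiority will be judged from the 95% CI of the between-group difference.

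The Objectives section begins: "Our study aims to assess the clinical effect of BSJY on pharmacogenomics and pro-inflammatory/anti-inflammatory cytokines in patients with low-to-medium-risk hypertension". It goes on to call the pharmacogenomic evaluation preliminary, and it also asks whether the combined treatment works better than Western medicine alone.

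Under Secondary outcomes, the cytokine entry reads "changes in the serum levels of TNFα, IL2R, IL6, IL8, IL10, and IL1β will be assessed at baseline and treatment endpoint" and the pharmacogenomic entry reads "twenty loci/SNPs associated with BP/hypertension will be assessed at baseline and treatment endpoint". Heart rate variability, a TCM score, SF-36 and four lipids are listed there too.

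On what the trial will show, the Introduction says: "If positive, this work will be the first one that provides an evidence-based medicine remedy for TCM on treating hypertension by pharmacogenomic evaluation". The Discussion says the trial "will provide high-powered evidence regarding the efficacy, safety, and pharmacogenomic evaluation of BSJY". Both the Strengths and limitations section and the limitations paragraph of the Discussion concede that finding genes associated with blood pressure needs much larger samples. The Sample size calculation uses a blood pressure effect of 4.5 mmHg and an SD of 10 mmHg, and nothing else.

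**The concern.** There are two linked problems.

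First, the article does more than leave multiplicity unmentioned. It states a rule under which any test below 0.05 is significant, and that rule reaches the twenty SNPs and six cytokines that the Objectives put in the aim. Applied as written, it makes a chance finding in those groups considerably more likely than 5%.

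Second, the article gives the pharmacogenomic part two incompatible standings. In the Objectives and the stated limitations it is preliminary and short of sample. In the Discussion it is high-powered. The sample size supports the first description only.

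What is at stake is how a single SNP below 0.05 would be read at the end: as a lead to follow up, or as well-powered evidence.

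**Working it through.** **1. Reproduce the plan's own figure.** Inputs from Sample size calculation: σ = 10, δ = 4.5, uα = 1.96, uβ = 1.282, c = 1.

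n per group = [(1.96 + 1.282) × 10 / 4.5]² × 2 = 103.8, so 104. Total 208, and 208 / (1 − 0.20) = 260. This agrees with the article. The calculation is for one blood pressure comparison between arms. It contains no SNP, no interaction and no cytokine, so the 90% power does not carry over to them.

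**2. Per-test error.** The text supports two readings: one-sided 0.05 (the significance sentence) or one-sided 0.025 (the lower tail of a 95% CI, which also matches uα = 1.96). Both are carried through.

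**3. Number of tests.** Cytokines: k = 6, listed by name. SNPs: k = 20, assuming one test per SNP against one blood pressure response. The article does not describe the SNP test, so this count is an assumption.

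**4. Chance of at least one false positive when nothing is affected.**

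- Independent tests: 1 − (1 − α)^k.
- Common correlation ρ: 1 − ∫ Φ((z₁₋α − √ρ·z)/√(1 − ρ))^k φ(z) dz.

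The document gives no correlations, so 0, 0.5 and 0.8 are assumed values.

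| Group | α per test | ρ = 0 | ρ = 0.5 | ρ = 0.8 |
|---|---|---|---|---|
| 20 SNPs | 0.05 | 64.2% | 33.9% | 19.0% |
| 20 SNPs | 0.025 | 39.7% | 21.0% | 11.2% |
| 6 cytokines | 0.05 | 26.5% | 18.6% | 12.6% |
| 6 cytokines | 0.025 | 14.1% | 10.4% | 6.9% |

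Worked example: 1 − 0.95²⁰ = 0.642 and 1 − 0.95⁶ = 0.265. The expected number of false positives among the SNPs is 20 × 0.05 = 1.0, or 20 × 0.025 = 0.5.

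**5. Effect of the proposed control.** The first Holm step across twenty SNPs is 0.05/20 = 0.0025, and across six cytokines 0.05/6 = 0.0083. At 0.0025 per test, twenty independent tests give 1 − 0.9975²⁰ = 4.9%.

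**The case against.** The strongest objection is that a condensed article commonly leaves multiplicity of secondary outcomes to the SAP, which is not shown, and that a 0.05 threshold is a generic convention. This stands as far as mere absence goes: not printing a hierarchy or correction is no error here. It does not dispose of the point, because the article states a rule for all tests, and an SAP that corrected or demoted the secondary outcomes would have to depart from that sentence.

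Several stronger readings are tempting, but the documents do not support them:

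- *That the secondary outcomes have no standing below the primary.* They are labelled secondary, and the trial is sized on blood pressure.
- *That pharmacogenomics carries no hedge.* It is called preliminary, and the need for larger samples is conceded twice. The fault is that these hedges contradict the claim of high power.
- *That cytokines carry a confirmatory claim.* They are named in the aim, but neither the success sentence in the Introduction nor the power sentence in the Discussion mentions them.
- *That one SNP below 0.05 would by itself count as a positive trial.* The Introduction does not define positive, and no section says this.
- *That the whole list of 33 items (6 + 4 + 1 + 1 + 1 + 20) has a 70% to 82% false-positive chance.* That range treats the SNPs as independent throughout. With a common correlation of 0.5 or 0.8 across all 33 at one-sided 0.05, the figure is 41% or 22%.

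It is also fair to say that inherited genotype does not change with treatment. The SNPs are therefore effect modifiers rather than outcomes that can differ between arms because of treatment, and the real number of tests could be smaller or larger than twenty. Correcting ordinary secondary outcomes such as lipids, SF-36 or the TCM score is a trade-off, not an obligation.

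**Conclusion.** The point holds in this limited form. The article fixes one uncorrected significance rule for every test, names pharmacogenomics and cytokines in its aim, and promises high-powered pharmacogenomic evidence that its own caveats and its BP-only sample size contradict.

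Over the assumed correlations, the chance of at least one false SNP finding is 19% to 64% at one-sided 0.05 and 11% to 40% at one-sided 0.025. For the cytokines it is 13% to 27% and 7% to 14%. All these figures exceed 5%, although the lowest (6.9% for cytokines, one-sided 0.025, correlation 0.8) does so only modestly. They rest on a global null, one test per SNP and an equal correlation within each group.

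The primary blood pressure result is not affected. What changes is what the trial may conclude from its secondary outcomes, above all the SNPs.

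**What to change.** 1. In Planned data analysis, confine the significance statement to the primary comparison. Report secondary outcomes as supportive, with between-arm differences and confidence intervals.
2. If a pharmacogenomic claim is kept, specify SNP-by-treatment interaction tests, with Holm (first step 0.0025) or false-discovery-rate control across the twenty SNPs.
3. Holm across the six cytokines (first step 0.0083) is optional, and needed only if a cytokine claim is to be made.
4. In the Discussion, withdraw the high-power claim for pharmacogenomics and call that part hypothesis-generating, in line with the Objectives.

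The cost is wording and a few lines of analysis code, with no new patients or measurements. Trial status reports that recruitment continues and no analysis has been done, so the change can still be prespecified. The downside is that an isolated secondary result just under 0.05 can no longer be called significant.
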